### Data collection, analysis, and management

A paper case report form (CRF) will be designed for registration of clinical data and the study result. All data will be meticulously documented in real-time by an independent data recorder. Data will be securely stored in a password-protected computer to safeguard the patients’ confidentiality. The study will adhere closely to the principles of good clinical practice (GCP). A designated investigator will be responsible for collecting, filing, and transferring data, while another independently verifies the accuracy and safety of the information.

For screening failures (patients who were screened but not randomized), a screening failure form will be completed. Investigators must ascertain the reasons for the withdrawal, including withdrawal from study investigations, withdrawal due to adverse events, failure to attend, non-compliance, withdrawal of consent, or other reasons. Participants who withdraw or are withdrawn from the trial will not be replaced. Data on participants after withdrawal will be used and analyzed with the intention-to-treat (ITT) principle.

#### Data monitoring

There are no planned interim analyses for the primary end point, but an independent data and safety monitoring board (DSMB) will regularly review study accrual and unblinded safety data.

#### Safety evaluation

Safety assessments will be composed of monitoring vital signs during the study and observing and recording all adverse events (AEs) and serious adverse events (SAEs).

AEs, defined as all unfavorable/unexpected medical events that occur in patients, whether causally related to the study drugs or not, will be recorded and treated immediately. SAEs are defined as adverse medical events, such as death, life-threatening, permanent, or serious disability or loss of function, and prolonged hospitalization after the subject receives the investigational drug. SAEs will be reported to the Ethics Committee within 24 h. In addition, the researchers will purchase clinical trial insurance, which compensates for treating any harm that occurs during the study.

#### Study discontinuation criteria

This trial will be terminated under the following criteria: 1) clustered serious adverse events are related to intervention measurement with supportive evidence and 2) the administration, including the DSMB, requests that the trial be discontinued.

#### Risks and benefits

There are no additional risks in this study other than the potential risks of standard clinical practice. No participants will receive any direct benefits from the study nor any compensation for their participation.

#### Sample size

The PAED score, which has excellent sensitivity (91%) and specificity (98%), will be used to assess emergence delirium (Janssen et al., 2011). A previous study showed that the rate of emergence delirium in pediatric tonsillectomy and adenoidectomy during sevoflurane anesthesia was approximately 44% (Yang et al., 2022). Hence, a sample size of 72 patients will provide 80% power at a 0.05 level of significance to detect a 30% difference in the proportion of children who attain emergence delirium in each group. Estimating a 20% drop out rate, 90 children will be needed in this study (PASS 15.0).

### Statistical analysis

The statistical analysis will be based on the intention-to-treat principle, including all randomized patients, regardless of subsequent withdrawal or deviation from the protocol. The data will be analyzed by SPSS version 24.0 for Windows (SPSS Inc., Chicago, IL, United States). The normality of distribution of continuous variables will be tested by the one-sample Kolmogorov–Smirnov test. Continuous variables with normal distribution will be presented as the mean ± standard deviation (SD), while non-normal variables will be presented as the median (interquartile range). Continuous variables will be analyzed using the Student’s t-test or Mann–Whitney U test based on the distribution, and categorical variables will be analyzed by the chi-squared test or Fisher’s exact test. Since there is only one primary outcome and the secondary outcomes are considered exploratory, no subgroup analyses or any other additional analyses will be planned in this study. No corrections for multiplicity will be planned. All statistical tests are two-sided, and a *p*-value <0.05 will be considered significant.

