## Abstract

**Background:** Remimazolam, a new ultrashort-acting benzodiazepine, is becoming increasingly applied in general anesthesia. This study is designed to investigate the effect of remimazolam-based total intravenous anesthesia and sevoflurane-based inhalation anesthesia on emergence delirium in pediatric tonsillectomy and adenoidectomy.

**Methods and analysis:** This is a monocentric, prospective, randomized, double-blind clinical trial. A total of 90 pediatric patients will be randomized to receive remimazolam-based total intravenous anesthesia (remimazolam group, n = 45) or sevoflurane-based inhalation anesthesia (sevoflurane group, n = 45). The primary outcome will be the incidence of emergence delirium, which will be evaluated using the Pediatric Anesthesia Emergence Delirium (PAED) scale. The secondary outcomes include the extubation time, recovery time, behavior change using the post-hospitalization behavior questionnaire for ambulatory surgery (PHBQ-AS), and adverse events.

**Ethics and dissemination:** This study has been approved by the Institutional Review Board (IRB) of the Second Affiliated Hospital and Yuying Children’s Hospital of Wenzhou Medical University (2023-K-262-02).

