### Random and binding

Since inclusion and exclusion criteria are carefully designed to limit potential bias, simple randomization will be conducted. Randomization will be performed in a 1:1 ratio according to a computer-generated randomization table (SPSS Inc., Chicago, IL, United States) at the beginning of the study.

The research team will be divided into two independent cohorts: anesthesia implementation researchers and postoperative assessment researchers. Postoperative assessment researchers will not be involved in the implementation and management of anesthesia and be blinded to the study allocation. Unblinding will not be carried out until after the completion of the study when all data will have been entered and the statistical analysis plan will have been confirmed.

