#### Secondary outcomes

The secondary outcomes will include the following:1) Extubation time: the time interval from the end of the surgery to extubation.2) Recovery time: the time interval from the end of the surgery to spontaneous eye opening in the PACU.3) The pain score will be assessed by the Face, Legs, Activity, Cry, and Consolability scale (FLACC, Supplementary Table S4). The FLACC scale has been proven to be a reliable instrument for assessing postoperative pain in children (from birth to 18 years) who have undergone outpatient surgery under general anesthesia (Crellin et al., 2015).4) The incidence of rescue propofol or fentanyl in the PACU.5) Behavior change will be assessed by the post-hospitalization behavior questionnaire for ambulatory surgery (PHBQ-AS, Supplementary Table S5) at 3 days. The PHBQ-AS has been validated in children aged 2–7 years (Lee-Archer et al., 2022).6) The satisfaction scores of the surgery doctor and attending anesthesiologist will be assessed after surgery by a 3-point scale: very satisfied, satisfied, and dissatisfied.7) Adverse events (AEs):i. Respiratory adverse events:a. Minor adverse events: oxygen desaturation (SpO_2_<90%), airway obstruction, coughing, or wheezing.b. Major adverse events: laryngospasm and bronchospasm.ii. Cardiovascular adverse events: hypotension (SBP <70 mmHg +2 times age) and bradycardia (HR < 70 beats. min^-1^).iii. Other adverse events: post-operative nausea, vomiting, etc.

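### The t-test branch for continuous outcomes assumes equal variances, although neither the normality check nor simple randomization protects it; Welch's test would be a free, minor improvement

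*Protocol article*

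**What the plan says.** All references are to the protocol article.

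- **Test.** Statistical analysis: "Continuous variables will be analyzed using the Student’s t-test". With its alternative, the sentence reads: "Continuous variables will be analyzed using the Student’s t-test or Mann–Whitney U test based on the distribution". No version for unequal variances is mentioned.
- **Selection rule.** Same section: "The normality of distribution of continuous variables will be tested by the one-sample Kolmogorov–Smirnov test". This is the only stated criterion for choosing between the two tests.
- **Allocation.** Random and binding: "simple randomization will be conducted", and "Randomization will be performed in a 1:1 ratio according to a computer-generated randomization table". Neither blocking nor any other restriction is described.
- **Arm sizes.** The Abstract gives "remimazolam group, n = 45" and "sevoflurane group, n = 45".
- **Outcomes that could be affected.** Secondary outcomes include extubation time, defined as "the time interval from the end of the surgery to extubation", and recovery time, which runs from the end of surgery to spontaneous eye opening. The Statistical analysis section treats secondary outcomes as exploratory and applies a two-sided 0.05 threshold to all tests.

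**The concern.** Student's t-test pools the two sample variances. With equal arms, the pooled standard error is right on average even if the SDs differ. With unequal arms it is not: it is too small when the smaller arm is the more variable, and too large when the larger arm is. The test is then too liberal or too conservative.

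Two features of the plan leave this open. A normality check looks at shape, so two normal samples with very different SDs pass it. Simple randomization at 1:1 does not deliver the 45 per arm given in the Abstract.

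The times to extubation and eye opening follow two different anesthetics, each titrated within a range, so different spread is plausible, though the article does not establish it. At stake is the nominal 5% level of any such comparison that reaches the t-test branch. These two outcomes show whether the new regimen changes wake-up time.

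**Working it through.** **Inputs.** From the article: 90 children, 1:1 simple randomization, two-sided 0.05, Student's t-test if normal. Assumed, because the article gives no SDs: SD ratios of 1.5 and 2 (3 as an extreme), normal data and equal means. The article states no figure of its own for this comparison, so there is none to reproduce.

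**Step 1: how unequal will the arms be?** The size of one arm is Binomial(90, 0.5).
- P(exactly 45/45) = 8.4%.
- P(40/50 or worse) = 2 × P(X ≤ 40) = 34.3%. This covers both directions; a given arm is the smaller one in half of it, about 17%.
- The central 95% range for one arm is 36 to 54.

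**Step 2: why the pooled test goes wrong.** Let the more variable arm have SD r and size n₁, and the other SD 1 and size n₂.
- True variance of the mean difference: V = r²/n₁ + 1/n₂.
- Expected pooled estimate: E = [((n₁−1)r² + (n₂−1)) / (n₁+n₂−2)] × (1/n₁ + 1/n₂).

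For r = 2:
- n₁ = 40, n₂ = 50: V = 4/40 + 1/50 = 0.120; E = (205/88) × 0.045 = 0.105; V/E = 1.14. The standard error is understated, so the test is liberal.
- n₁ = 50, n₂ = 40: V = 4/50 + 1/40 = 0.105; E = (235/88) × 0.045 = 0.120; V/E = 0.87. It is overstated, so the test is conservative.
- n₁ = n₂ = 45: V = 5/45 = 0.111; E = 2.5 × 2/45 = 0.111; V/E = 1. No distortion.

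**Step 3: size of the error.** Simulated type I error of Student's test at nominal 5% (60,000 replicates per cell):

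| Split | SD ratio | Smaller arm more variable | Larger arm more variable |
|---|---|---|---|
| 40/50 | 1.5 | 6.0% | 4.2% |
| 40/50 | 2 | 6.9% | 3.7% |
| 36/54 | 1.5 | 7.0% | 3.6% |
| 36/54 | 2 | 8.3% | 2.7% |

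Repeat runs at 40/50 and ratio 2 gave about 6.8% and 3.7–3.8%. At 45/45 the error is 4.9–5.2% for ratios from 1 to 3. Welch's test gave 4.8–5.2% in every cell tried.

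**Step 4: averaged over the design.** Weighting each split by its binomial probability, with N = 90, Student's error is 5.1% (ratio 1.5), 5.2% (ratio 2) and 5.4% (ratio 3). If only 72 children are evaluable, it is 5.1%, 5.3% and 5.5%.

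**Step 5: price of Welch.** With equal SDs, a standardized difference of 0.6 and a 40/50 split, power was 79.8% for both tests in one run. In a second run (200,000 replicates) it was 79.9% against 79.9%, a loss of 0.07 point.

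**The case against.** The case against is substantial.

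- **The plan does not commit these times to Student's test.** A reader might infer that extubation and recovery time will be compared with the t-test. The sentence goes on to offer Mann–Whitney for non-normal variables, and times are often skewed. This stands: the error rates above describe the t-test branch only. It does not remove the point, because that branch may well be reached. In a simulation with assumed gamma data (shapes 4 and 2), one sample of 45 passed an uncorrected Kolmogorov–Smirnov test about 98% and 93% of the time. With the Lilliefors correction it passed about 63% and 36%. The article does not say which form is meant.
- **No interval is at fault.** A reader might also infer that planned confidence intervals will be wrong. The Statistical analysis section describes summaries and p-values and plans no interval for these outcomes, so the documents do not support that.
- **Over the whole design the 5% level nearly holds.** An average error of 5.0–5.5% does not support a claim that it is materially broken. This stands. However, the trial is analysed once, at a split known by then, and at that split the error is larger and avoidable.
- **Unequal spread is assumed.** This stands, which is why a range is shown.
- **The outcomes are exploratory, and detail may sit in an unseen analysis plan.** The first part stands and limits the weight of the point. On the second, the article does name a test, so suggesting a better one addresses stated text. An unseen plan may already do the same.

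**Conclusion.** The point holds as a minor, free improvement and not as an error that threatens the trial. The t-test branch assumes equal variances, no stated rule addresses spread, and simple randomization does not secure equal arms.

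Three conditions must coincide before it matters: the outcome passes the normality check, the SDs differ, and the realized arms are unequal. At 40/50 the true error is then about 6.0% or 4.2% at an SD ratio of 1.5, and about 6.8% or 3.7% at a ratio of 2. The direction depends on which arm is more variable. These figures rest on normal data and assumed SD ratios.

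The primary outcome is binary and is not affected, and neither is the sample size.

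**What to change.** In the Statistical analysis section, replace *Student's t-test* with *Welch's t-test (unequal variances)* in the t-test branch, and leave the Mann–Whitney branch as it stands.

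This is a change of wording only. It needs no new data, does not alter the number of children and costs under 0.1 point of power if the SDs are equal. It should be made before unblinding, so that the choice of test cannot depend on the results.

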### Intervention

#### Preoperative period

All children will be confirmed to meet the ASA fasting guideline. Demographic and baseline data will be obtained by a member of the research team. No premedication will be given before anesthesia. To mitigate preoperative anxiety and facilitate the completion of venipuncture before anesthesia induction, children will be allowed to watch cartoon videos in the presence of one of their parents or guardians. During the preoperative period, an independent researcher will assess the anxiety level by using the modified Yale Preoperative Anxiety Scale (m-YPAS, Supplementary Table S1).

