The association of benzodiazepines with the occurrence of emergence delirium remains to be discussed. Nevertheless, recent studies have reported that remimazolam is associated with a decreased incidence of emergence delirium (Duan et al., 2023; Yang et al., 2023). A study conducted by Duan et al. found that remimazolam not only effectively reduced the incidence of ED compared with propofol but also demonstrated minor hemodynamic effects and a lower occurrence of postoperative adverse events in geriatric hip-replacement patients (Duan et al., 2023). Yang et al. demonstrated that older adult patients undergoing general anesthesia with remimazolam had a low incidence of emergence delirium, similar to propofol (Yang et al., 2023). In the pediatric population, a study found that a single bolus of remimazolam 0.2 mg kg^-1^ at the end of the surgery resulted in a significantly lower incidence of emergence delirium (from 44% to 12%) after sevoflurane anesthesia (Yang et al., 2022).

This study will control for and assess confounders of ED in children, such as the type of surgery, age, patient anxiety, pre-existing behaviors, and interactions with healthcare providers (Mason, 2017). Although the assessment of preoperative anxiety levels has often been overlooked in previous studies, it is noteworthy that in pediatric patients with preoperative anxiety, the reported incidence of postoperative delirium was 3.5 times higher than in non-anxious individuals (Choi et al., 2022). This study will utilize m-YPAS for evaluating preoperative anxiety levels in children. In addition, to address the challenge of blinding due to different anesthesia methods during surgery, we will ensure the integrity of blinding efficacy by having postoperative assessors who are not involved in intraoperative management.

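### The Discussion says patient anxiety will be controlled for, but the analysis plan fixes unadjusted tests and rules out others, so the measured anxiety score plays no part in estimating the treatment effect

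*Protocol article*

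**What the plan says.** Five places in the protocol article bear on this.

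- **Discussion, on confounders:** "This study will control for and assess confounders of ED in children, such as the type of surgery, age, patient anxiety, pre-existing behaviors", followed by interactions with healthcare providers. For children with preoperative anxiety it adds that "the reported incidence of postoperative delirium was 3.5 times higher than in non-anxious individuals". The stated use of the score is: "This study will utilize m-YPAS for evaluating preoperative anxiety levels in children".
- **Preoperative period:** "an independent researcher will assess the anxiety level by using the modified Yale Preoperative Anxiety Scale". The same paragraph describes a measure against anxiety for all children: "children will be allowed to watch cartoon videos in the presence of one of their parents or guardians". No premedication is given.
- **Inclusion criteria:** age is limited to 3–6 years and every child has the same type of operation. Neither the inclusion nor the exclusion criteria mention anxiety.
- **Random and binding:** "simple randomization will be conducted", on the ground that the eligibility criteria already limit bias. Unblinding waits until the statistical analysis plan has been confirmed.
- **Statistical analysis:** "categorical variables will be analyzed by the chi-squared test or Fisher’s exact test", which covers the binary primary outcome (PAED of 10 or more). No covariate is named, and "no subgroup analyses or any other additional analyses will be planned in this study".

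**The concern.** The Discussion presents anxiety as a strong predictor of the primary outcome that other studies have overlooked, and says this study will control for it. A reader would expect anxiety to enter either the allocation or the analysis. It enters neither: there is no stratification, and the tests take no covariate.

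This is not mere silence that a separate analysis plan could fill. The Statistical analysis section closes the list, so a later plan that adjusted for m-YPAS would depart from the published protocol. The reason given there, a single primary outcome with exploratory secondary outcomes, concerns multiplicity and does not argue against covariate adjustment of the primary comparison.

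Two things are at stake. Some power is given up although the covariate is already collected. And if the arms differ in anxiety by chance, any adjusted analysis will be post hoc and open to dispute.

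**Working it through.** **1. The plan's own figure.** Inputs from Sample size: 44% with sevoflurane, a 30-point difference (so 14%), 80% power, 0.05; two-sided, from Statistical analysis. With pooled variance and a mean rate of 0.29:

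n per arm = [1.96·√(2·0.29·0.71) + 0.8416·√(0.44·0.56 + 0.14·0.86)]² / 0.30² = [1.96·0.6417 + 0.8416·0.6056]² / 0.09 = 34.7, so 35 per arm, 70 in all.

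The stated 72 is within two patients of this, and 72/0.8 = 90. Power at 36 per arm is 81.5%, and at 45 per arm 89.4%. The sample size thus rests on an unadjusted comparison, which is adequately powered on these inputs. This refers to the chi-squared test. Fisher's exact test would have 75.2% at 36 per arm and 85.2% at 45, but with 36·0.29 = 10.4 expected events per arm, chi-squared is the natural choice.

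**2. Power gained by using anxiety.** The prevalence of anxiety is not in the documents, nor is it clear whether the 3.5 is a risk ratio or an odds ratio. Both readings were tried, with anxiety as a yes/no factor.

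| Assumption | Method | Total n | Unadjusted | Using anxiety |
|---|---|---|---|---|
| Risk ratio 3.5, 50% anxious | Mantel-Haenszel | 72 | 81.6% | 85.7% |
| | | 90 | 89.4% | 93.4% |
| Odds ratio 3.5, 50% anxious | Mantel-Haenszel | 72 | 82.4% | 84.6% |
| | | 90 | 89.4% | 90.5% |
| Odds ratio 3.5, 30% anxious | Logistic | 72 | 82.5% | 85.9% |
| | | 90 | 90.2% | 91.9% |
| Odds ratio 3.5, 50% anxious | Logistic | 72 | 83.0% | 86.1% |
| | | 90 | 89.6% | 91.3% |

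The Mantel-Haenszel rows use 5,000 simulated trials each and the logistic rows 3,000. At 3,000 runs the simulation error is about √(0.82·0.18/3000) = 0.7 points per estimate. In the logistic runs, type I error was 4.2–5.1% unadjusted and 4.9–5.7% adjusted. A separate simulation of the method proposed below (logistic regression on continuous anxiety and age, standardised to a risk difference, with assumed effect sizes) gave a gain of about 1 to 5 points with type I error near 5%.

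**3. Chance imbalance.** With 45 per arm and 50% anxious, the SD of the difference in anxious proportions is √(0.25·2/45) = 0.105. The probability of a difference of at least 10 points in either direction is 2·[1 − Φ(0.10/0.105)], about 34%. In the logistic simulations a difference of at least 15 points occurred in about 13–20% of trials.

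**4. What an imbalance does to the crude difference.** Take 44% v 14%, 50% anxious, and a 10-point imbalance split evenly between the arms.

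- *Risk ratio 3.5.* Risks in non-anxious and anxious children are 0.44/2.25 = 0.196 and 0.684 on sevoflurane, and 0.14/2.25 = 0.062 and 0.218 on remimazolam. Shift = 0.05·(0.488 + 0.156) = 0.032.
- *Odds ratio 3.5.* Solving for the stratum risks that average 0.44 and 0.14 gives 0.291 and 0.589, and 0.070 and 0.210. Shift = 0.05·(0.299 + 0.139) = 0.022.

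Each 10 points of imbalance therefore moves the crude difference by about 2 to 3 points, towards either arm.

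**The case against.** The strongest reply is that controlling for a factor need not mean regression. The Discussion's list starts with type of surgery, which cannot be a covariate when every child has the same operation. Age is restricted to 3–6 years, mental disorder is excluded, and anxiety is mitigated in both arms by cartoons and a parent's presence. On that reading the sentence promises design control plus measurement. This largely stands for surgery type and partly for age. It is weaker for anxiety: mitigation in both arms lowers the level but neither balances nor adjusts for what remains, and eligibility does not restrict it.

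Three stronger readings are tempting, and the documents support none of them.

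- *The unadjusted result would be biased by anxiety.* It would not. Under randomization, chance imbalance is already covered by the test's error rate, and the simulated type I error is close to 5%.
- *The m-YPAS data are wasted, or nothing controls anxiety.* The score can still describe baseline comparability, which meets the promise to assess, and the mitigation measure is part of the protocol.
- *Pre-existing behaviour is not measured.* The article says baseline data are collected without itemising them. A condensed article may leave the instrument out.

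One might also infer a shift of about 5 points per 10 points of imbalance (0.10·0.488). That holds only if both arms carry sevoflurane-level risk, not under the planned 44% v 14%.

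It is also fair that an unadjusted primary test matches the sample-size basis, and that events are few: 36·(0.44 + 0.14) = 20.9 expected in 72 children, about 5 of them on remimazolam. That calls for a small model. It does not rule one out, since the simulated adjusted method held its error rate.

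**Conclusion.** The concern holds as a mismatch between the Discussion and the Statistical analysis section, together with a small, avoidable loss of efficiency. It is clear for anxiety, weak for age, and absent for surgery type. The planned test is valid and adequately powered on the plan's own inputs. The cost of ignoring m-YPAS is about 1 to 5 points of power at 72 to 90 children, plus the lack of a prespecified answer to an imbalance in anxiety. These figures rest on assumptions the documents do not settle: 30% or 50% of children anxious for the power gain, 50% for the imbalance figures, and the 3.5 read as an odds ratio or a risk ratio. A weaker link between m-YPAS and delirium in this setting would shrink the gain. The change is worth making because it is cheap, not because the primary result is in danger.

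**What to change.** **Statistical analysis section.** Before unblinding, prespecify an analysis of emergence delirium adjusted for continuous m-YPAS score and age: logistic regression standardised to a risk difference with 95% CI. Preferably make this the primary analysis and keep the unadjusted chi-squared test as supporting. At the least, include it as a prespecified sensitivity analysis. Amend the sentence that excludes additional analyses to match, and keep the model to these two covariates given the small number of events.

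**Discussion.** State which factors are controlled by design (surgery type, age range), which by adjustment (anxiety, age), and which are not adjusted for.

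**Cost.** Wording in the protocol and analysis plan only. m-YPAS and age are already collected and the sample size need not change. Recruitment began on 1 April 2024, so date the amendment and record that it was made blind to allocation. The rule that unblinding waits for a confirmed analysis plan leaves room for this.
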